#### Data collection and storage

Data will be collected annually via the UK-based digital registries and as negotiated with the international sites (where applicable). No data will be exported outside the EU or the UK. Data collected from international sites will be stored according to the terms outlined in the DSA.

Long-term follow-up data received from national registries will be processed and held on a secure Barts Cancer Centre IT network. Data registry variables specified in Table 1 will be used to capture breast cancers, deaths, other cancers, cardiovascular, cerebrovascular, and fractures to meet the study objectives. Supplemental information on tumour markers will be collated from national and devolved cancer registry datasets (Table 2).

**Table 1. Events of Interest/ICD code**

| Event                       | ICD-code                                                                                 |
|-----------------------------|------------------------------------------------------------------------------------------|
| Breast cancer               |                                                                                          |
| Breast cancer (invasive)    | C50.0-9                                                                                  |
| Breast cancer (DCIS)        | D05.0/1/7/9                                                                              |
| Other malignant cancer      | C00-43, C45-49 and C51-97 (all sub-codes)
This includes all other cancers except skin |
| Other events                |                                                                                          |
| Pulmonary embolism          | I26.0, I26.9                                                                             |
| Deep vein thrombosis        | I80.2                                                                                    |
| Cerebrovascular events      | I63 (all sub-codes), I64                                                                 |
| Cardiac arrest              | I46 (all sub-codes)                                                                      |
| Acute myocardial infarction | I21 (all sub-codes), I22 (all sub-codes)
I22 is for subsequent myocardial infarctions |
| Heart failure               | I50 (all sub-codes)                                                                      |

|                                     |                                                                                                                                                                                                                                                             |
|-------------------------------------|-------------------------------------------------------------------------------------------------------------------------------------------------------------------------------------------------------------------------------------------------------------|
| Transient cerebral ischaemic attack | G45.8, G45.9                                                                                                                                                                                                                                                |
| Hypertension                        | I20, I15 (all sub-codes), I27 (all sub-codes)                                                                                                                                                                                                               |
| Fractures                           | M80 (all sub-codes), T02.9, T08, T10, T12, S02 (all sub-codes), S12 (all sub-codes), S22 (all sub-codes), S32 (all sub-codes), S42 (all sub-codes), S52 (all sub-codes), S62 (all sub-codes), S72 (all sub-codes), S82 (all sub-codes), S92 (all sub-codes) |

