#### **1.2 Secondary**

- 1) To examine the role of anastrozole in preventing oestrogen receptor positive breast cancer.
- 2) To examine the effect of anastrozole on other cancers, cardiovascular disease, fracture rates, and non-breast cancer deaths.
- 3) To examine tolerability and acceptability of side effects experienced by women on the study. (Met at LPLT – March 2017).

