**Table 3. Digital registry sources of variables**

| Data source                                                 | Variables                                                         | Information provided                                                                                                            |
|-------------------------------------------------------------|-------------------------------------------------------------------|---------------------------------------------------------------------------------------------------------------------------------|
| Hospital Episode Statistics (HES) data set variables | GP Code
Date of diagnoses
Date of diagnoses
Description  | GP contact details
Cardiovascular and cerebrovascular events, new and recurrent breast cancers other cancers, bone fractures |
| Cancer registry data set variables                   | Date of diagnoses
Diagnoses Code
Description                | New and recurrent breast and other cancers including melanomas                                                                  |
| Civil Registration Mortality data set variables      | IBIS-II
Status

Date of Death

Cause of death      | Death and cause of death                                                                                                        |
| Public Health England data set variables             | Cancer registry - patient table
Cancer registry - tumour table | Supplemental data on tumour markers. TNM staging and grading, ER, PR and HER status of breast cancers                           |

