### **SAEs during the follow up period:**

SAEs which are an event of interest (see section 4.5.1.2), should continue to be collected and reported to the IBIS-II CCO after a patient has completed active treatment i.e. during the annual post-treatment follow-up period by the PI/delegated clinician under expedited timeframes. AEs/SAEs in clinical areas other than those pre-specified will not be actively sought or collected within CRFs during the follow up period and should not be sent to IBIS-II CCO. However, if an investigator becomes aware of a SAR during the follow up period i.e. meets the definition of an SAE and in the investigator's judgement has a causal relationship to a study IMP, this should be reported by the investigator to the IBIS-II team using expedited reporting timeframes, regardless of whether the SAE is a clinical event of interest.

What to report as an SAE in the long term follow up period under expedited conditions:

- ✓ Cerebrovascular event/Stroke/TIA
- ✓ New primary cancers (except basal cell carcinoma, squamous cell carcinoma of the skin and carcinoma in situ of the cervix)
- ✓ Cardiovascular events e.g. angina, myocardial infarction
- ✓ Thromboembolic events e.g. deep vein thrombosis, pulmonary embolism, phlebitis
- ✓ Osteoporosis/Broken/fractured bone
- ✓ Deaths (including underlying cause of death)
- ✓ Any other AE meeting the definition of serious (see above) and in the opinion of the investigator is causally related to the IMP i.e. **all SARs**

What not to report as an SAE in the long term follow up period:

- ✗ New breast cancer or DCIS (endpoint not SAE)
- ✗ AEs that do not meet the definition of serious
- ✗ Pre-planned hospitalisations/elective surgery where the underlying condition does not meet the definition of an SAE
- ✗ Non-protocol specified SAEs (see above) that are not in the opinion of the investigator, related to the IMP

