### **Closed UK sites**

There are limitations of registry data collection, in that seriousness and relatedness cannot be assessed by this method of data collection once the sites have closed. A risk adapted approach is now merited as the safety profile of anastrozole is well-established across multiple trials and long follow up periods (as of 31 July 2016, the total cumulative exposure

figure for Arimidex (anastrozole) in the marketed setting is calculated to be in excess of 8 million patient years). Anastrozole has also been recommended by the National Institute of Clinical Excellence (CG164) as a first-line therapy for women at risk of breast cancer without osteoporosis. All participants are now off-treatment and the half-lives of anastrozole is relatively short (50 hours), therefore collection of follow up data from the digital registries poses a minimal risk to participants.

All data received via registries in the UK will be assessed by the data management (DM) team as part of a bulk dataset. This long-term follow-up data will be received by an independent data manager on a yearly basis from the various devolved UK data registries and Public Health England as previously described. The data will be screened for deaths, new and recurrent breast cancers and other ICD-coded events listed in Table 1. All newly identified events that meet the criteria listed in 4.5.1.2 will be sent to AZ as an 'unverified' line listing once a year. This will provide data on AEs that should be reported in the long term follow up period under expedited conditions but with the limitations discussed above.

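### The registry code range for other malignant cancers takes in the secondary-neoplasm codes C77-C79 and C80, so breast-cancer spread can be counted as an other cancer

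*Protocol*

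**What the plan says.** Section 1.2 sets the secondary aim: "To examine the effect of anastrozole on other cancers, cardiovascular disease, fracture rates, and non-breast cancer deaths".

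Section 4.5.1.4 (Data collection and storage) says that the Table 1 variables "will be used to capture breast cancers, deaths, other cancers, cardiovascular, cerebrovascular, and fractures to meet the study objectives". Table 1 gives the codes for other malignant cancer as "C00-43, C45-49 and C51-97 (all sub-codes", with the note "This includes all other cancers except skin".

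Table 3 lists what each source supplies. Hospital Episode Statistics (HES) are to give, among other events, "new and recurrent breast cancers other cancers, bone fractures". The cancer registry is to give "New and recurrent breast and other cancers including melanomas".

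For closed UK sites, Section 4.5.4.3 says: "The data will be screened for deaths, new and recurrent breast cancers and other ICD-coded events listed in Table 1". Under the heading on the scope of UK registry data collection, the registries become the only source once a UK site has closed.

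Site reporting is narrower. Section 4.5.4.2, on the follow-up period, lists as reportable "New primary cancers (except basal cell carcinoma, squamous cell carcinoma of the skin and carcinoma in situ of the cervix". Section 4.5.4.3, on open UK sites, likewise speaks of a new non-breast primary, and Section 6.2 speaks of cancer incidence.

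**The concern.** Table 1 works in ICD-10, and in that classification C77, C78 and C79 denote secondary malignant neoplasms and C80 a malignancy of unspecified site. They sit inside C51-97. A woman with breast cancer whose later hospital record carries one of these codes therefore meets the Table 1 definition of an other malignant cancer, although she has no new primary.

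The protocol states no rule that drops such a record or assigns it back to the breast cancer. The GP follow-up in Section 4.5.1.4 covers new or recurrent breast cancers only.

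The error would not fall evenly on the arms. Section 4.5.1.3 reports more breast cancers on placebo, so records of spread should arise more often there. On a secondary aim, that would look like protection by anastrozole against other cancers. The same event would also mean different things at an open site and in the registry extract.

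**Working it through.** **1. Code membership.** Expanding C00-43, C45-49 and C51-97 over C00 to C97 leaves out only C44 and C50. C77, C78, C79 and C80 are inside. So is C43 (melanoma), which agrees with Table 3.

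**2. The imbalance that the argument rests on.** Section 6.3 plans 78 placebo and 39 anastrozole breast cancers. This reproduces:
- Placebo: 1,750 women × 5 years × 9/1,000 = 78.75.
- Anastrozole: 1,750 × 5 × 4.5/1,000 = 39.4.
- Chi-square: (78 − 39)²/(78 + 39) = 13.0, as stated.

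The reported counts in Section 4.5.1.3 are 85 and 40.

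**3. Direction.** If a fraction m of breast cancers gains a secondary code in each arm, the false additions are 85m on placebo and 40m on anastrozole. They would be equal only if the fraction were 85/40 = 2.1 times as high on anastrozole.

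**4. Size, as illustration.** Let B be the true other cancers per arm, with no treatment effect. The apparent rate ratio is R = (B + 40m)/(B + 85m). The protocol gives neither m nor B, so both are varied.

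| m (assumed) | False, placebo | False, anastrozole | R, B = 50 | R, B = 100 | R, B = 150 |
|---|---|---|---|---|---|
| 5% | 4.25 | 2.0 | 0.959 | 0.978 | 0.985 |
| 10% | 8.5 | 4.0 | 0.923 | 0.959 | 0.972 |
| 20% | 17.0 | 8.0 | 0.866 | 0.923 | 0.946 |

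The shift in the test statistic is about (85m − 40m)/√(2B + 125m). At m = 10% and B = 100 it is 4.5/√212.5 = 0.31. Over the table it runs from 0.13 to 0.80.

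**5. Why the table leans high.** The counts 85 and 40 are trial-wide and include DCIS, which would seldom produce a secondary code. The defect acts mainly on UK registry follow-up. So m is really a product: the share of cases that are invasive and in registry follow-up, times the share of those that gain a secondary code. If only half the cases qualify, for example, a 10% coding fraction gives 10% × 0.5 = 5%, the first row.

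**6. Outer case.** Section 6.3 also names 208 long-term events and a 60% reduction. Split at a ratio of 0.4, that is 208 × 0.4/1.4 = 59 and 208/1.4 = 149. The same m and B then give R from 0.97 down to 0.78 and a shift of at most about 1.5. This is a planning scenario pushed to its extreme, not a forecast.

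**7. After the correction.** With C77-C79 not counted, their false additions are 0 in both arms and the null ratio returns to 1.00, provided that C80 records are also classified correctly.

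**The case against.** The best defence is that Table 1 is a capture list and not an analysis definition. Section 4.5.1.4 says the list is used to match events with the detail in Table 2, which includes site, histology and laterality, and that detail can separate a deposit from a new primary. The cancer registry is a source as well as HES. The SAP or the data management plan could hold the classification rule. A wide range also has a use: the protocol wants recurrent breast cancers, and no other row of Table 1 names codes for distant recurrence.

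Part of this stands. The documents do not show that metastases have been or will be counted as other cancers, and deleting C77-C79 from the extract could lose useful records. But Table 1 puts these codes under the label of other malignant cancer and ties them to the study objectives. Leaving detail to a later document does not repair a code list that the protocol itself fixes wrongly.

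Two further objections also carry weight. The expedited-reporting list in Section 4.5.4.2 is not an endpoint definition, although the incidence wording in Section 6.2 points the same way. Open UK sites verify newly identified registry events, so the exposure lies mainly with closed sites.

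A reader might also infer that the note about skin changes the counts. It does not: the explicit codes govern, with C43 in and C44 out. That agrees with Table 3 and with the exclusion of basal and squamous cell carcinoma elsewhere. The note is only loosely worded.

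**Conclusion.** The code range is wrong as written. The defect is minor to moderate. It touches one secondary endpoint, mainly through UK registry data, and leaves the primary endpoint alone, because that endpoint is locally histologically confirmed breast cancer under its own codes.

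Any misclassification would tend to favour anastrozole. That rests on the reported 85 against 40 breast cancers and on roughly similar coding fractions in the two arms. The second is an assumption, since the tumours that arise on treatment may differ in type.

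A reader might go on to infer a known bias of several percent in the other-cancers comparison. The documents do not support that. They give no fraction of cases with a secondary code, no count of other cancers, no account of how HES codes spread, and no split of the 85 and 40 by country or by invasive disease. The size cannot be established from the document and is probably small. Metastases of a non-breast cancer add little error if each woman is counted once.

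**What to change.** - Define the other-malignant-cancer row of Table 1 as a new non-breast primary: C00-C43, C45-C49, C51-C76 and C81-C97.
- Keep C77-C79 in the extract under a separate row for secondary neoplasm or possible recurrence, and state that it does not count as an other cancer.
- Classify C80 records by review blind to treatment, against the cancer-registry site and histology in Table 2. Do not make the rule depend only on whether the woman has had breast cancer, because treatment affects that.
- As a tidy-up, change the note so that it excepts only non-melanoma skin cancer (C44).

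The cost is a change to Table 1, a re-run of the code map and a blinded review of a few unknown-primary records. No new data need be requested from the registries.

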#### **4.5.1.2 Post-treatment Follow-up Questionnaires (PTQ) - Years 6 – 10**

After 5 years of active treatment, women will continue to be followed up for clinical events of interest including SAEs, via the 'post-treatment follow-up' CRF for a further 5 years.

These will specifically ask the patients about the following events: -

- Breast cancer and DCIS (endpoint not requiring reporting)
- Stroke or TIA
- Other cancers (except basal cell carcinoma, squamous cell carcinoma of the skin and carcinoma in situ of the cervix)
- Cardiovascular events e.g. angina, heart attack, hypertension
- Thromboembolic events e.g. deep vein thrombosis, pulmonary embolism, phlebitis
- Osteoporosis/Broken/fractured bone
- Deaths

The decision to collect events of interest rather than asking about all AEs is based upon the following

- 5x half-life of IMPs will be reached within 35 days i.e. a short time period and therefore long term monitoring is not required.
- Except for certain conditions (endometrial cancer, osteoporosis/fracture, cardiovascular disease), further side-effect either stop with IMP washout or are of negligible significance.
- The safety profiles of Anastrozole has already been well-established across multiple trials and long follow up periods (as of 31 July 2016, the total cumulative exposure figure for ARIMIDEX in the marketed setting is calculated to be in excess of 8 million patient years)
- This is an ageing trial population with many AEs meeting the definition of SAEs but that are not of direct relevance to the trial objectives. To date, approximately 6% of reported SAEs in the post-treatment phase have been defined as causally related by the site investigator. Efforts should be re-focused on the collection of events known to be IMP related and the identification of any emerging safety signals. A more defined scope of AE collection is therefore warranted.

- All identified SARs/SUSARS will meet expedited reporting timeframes.

Sites have the option to conduct this by clinic, phone, postal questionnaire or if the patient is not able to be contacted, consultation of hospital records. This will collect data required to meet the primary, secondary and exploratory objectives of the trial.

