### **Patient identifiable data and raw extracts**

PID including the participants full name, NHS number, date of birth and postcode is collected by the sites and stored on an encrypted table within the main study database. Section 7 details the consent procedure in place for collection of PID.

Raw data extracts received from the digital registries will either be sent linked to the IBIS-II study number and PID removed by the data registry beforehand or it will be sent containing PID. This will depend on the specific policy of the data organisation.

When PID is sent to the IBIS-II research team from a data registry, a suitably qualified person will pseudonymise the datasets by linking the data to the existing IBIS-II dataset and remove all PID prior to further processing by the IBIS-II data management team to minimise unmerited access to PID. All raw datasets are considered source data and should be stored for the duration of the study and archiving period. This data will be stored on an encrypted, un-networked computer at the Wolfson Institute of Preventive Medicine. The ICD-10 code list of events (Table 1) will be used to match events with further details on deaths, new or recurrent breast cancers from variables listed in Table 2.

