Antipyrine, warfarin and cimetidine clinical interaction studies indicate that the co-administration of anastrozole with other drugs is unlikely to result in clinically significant drug interactions mediated by cytochrome P450.

Hepatic changes (elevated gamma-GT or less commonly alkaline phosphatase) have been reported in patients with advanced breast cancer, many of whom had liver and/or bone metastases. A causal relationship for these changes has not been established. Slight increases in total cholesterol have also been observed in clinical trials with anastrozole.

Daily doses of anastrozole up to 10 mg do not have any effect on cortisol or aldosterone secretion, measured before or after standard ACTH challenge testing. Corticoid supplements are therefore not needed.

Events of Carpal Tunnel Syndrome have been reported in patients receiving anastrozole treatment in clinical trials in greater numbers than those receiving treatment with tamoxifen. However, the majority of these events occurred in patients with identifiable risk factors for the development of the condition.

In the ATAC trial, ischaemic cardiovascular events were reported more frequently in patients treated with anastrozole compared to those treated with tamoxifen, although the difference was not statistically significant. The observed difference was mainly due to more reports of angina pectoris and was associated with a sub-group of patients with pre-existing ischaemic heart disease.

Sensory disturbances (including paraesthesia, taste loss and taste perversion) have been reported more frequently in patients receiving anastrozole than those on tamoxifen in clinical trials. In order to ensure that participants still on treatment are aware of this

newly listed side effect (added to Arimidex Summary of Product Characteristics [SmPC] v160114), they must be informed of this at their next clinic appointment.

The full list of adverse reactions to anastrozole is available as a separate document. (Astra Zeneca Core Data sheet)

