### **6.2 Endpoints**

The primary endpoint is the development of locally histologically confirmed breast cancer, both invasive and non-invasive (i.e. including DCIS). The principal analysis for comparing the active treatment to placebo will be performed when 117 cases of breast cancer have been diagnosed in the prevention stratum (see section 6.3 for more details). It is anticipated that this will occur after a median follow-up of 5 years. Primary endpoint data will be collected from participating women until the end of trial definition (LPLT + 5 years of follow up).

Adherence to treatment protocol will cease if a woman develops breast cancer and a breast cancer CRF should be returned. All breast cancer pathology must be reviewed by a pathologist approved by the UK National Breast Screening Programme or foreign equivalent. In addition, a tissue block or where unavailable 20 sections. will be required in consenting women for all breast tumours developing after entry into the trial.

It is recognised that breast cancer mortality is an important exploratory endpoint and this will also be analysed. However, the power to detect this within 10 years is marginal. Continued long-term follow-up beyond 10 years, as well as an overview of other similar trials will be needed to obtain clear results on this question. Total and cause-specific mortality will be analysed and the Final CRF (if still on active treatment) and Death CRF should be returned for any woman who dies of any cause while on therapy.

All women will be followed up for cancer incidence (breast and other cancers) and cause of death using available NHS registries as described in section 4.5.1.4. During the 5-year period of active follow-up and the post-treatment follow-up period serious medical conditions will be recorded including myocardial infarction and other heart problems, thromboembolic events (superficial and deep), cardiovascular events, osteoporosis, fractures, and other cancers.

Basic information on prescriptions and hospital visits during the 5 years of active treatment for each participant will also be recorded.

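### Table 1, the ICD-10 list that screens registry data for closed UK sites, does not match the protocol's own events of interest, and its hypertension row needs correcting on either reading

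*Protocol*

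**What the plan says.** Table 1 is the working filter for registry data. Section 4.5.1.4, under patient identifiable data and raw extracts, says: "The ICD-10 code list of events (Table 1) will be used to match events". The scope paragraph of the same section makes the registries the only long-term source once a UK site closes. Section 4.5.4.3 (closed UK sites) screens the yearly extracts for deaths, breast cancers and the coded events of Table 1. It then undertakes to list to the drug supplier, once a year, the new events that meet 4.5.1.2.

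The events of interest are set out elsewhere. Section 4.5.1.2 names:
- "Cardiovascular events e.g. angina, heart attack, hypertension"
- "Thromboembolic events e.g. deep vein thrombosis, pulmonary embolism, phlebitis"
- "Osteoporosis/Broken/fractured bone"
- stroke or TIA, without restriction by type.

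Section 4.5.4.2 repeats angina, phlebitis, osteoporosis and stroke for expedited reporting in follow-up. Section 6.2 has serious conditions recorded through treatment and post-treatment follow-up, among them "thromboembolic events (superficial and deep), cardiovascular events, osteoporosis, fractures, and other cancers".

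In Table 1 the hypertension row is "I20, I15 (all sub-codes), I27 (all sub-codes", with the closing bracket after the last word. The venous rows are pulmonary embolism (I26.0, I26.9) and deep vein thrombosis (I80.2). The cerebrovascular row is I63 and I64. The only bone row is fractures, which begins "M80 (all sub-codes), T02.9, T08, T10, T12".

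**The concern.** For a closed UK site, an event with no code in Table 1 is not picked up, and no site form exists to recover it. Section 4.5.4.3 screens on one list and promises to report on a wider one, so the yearly listing cannot deliver what it promises.

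The affected events matter to the protocol. Cardiovascular disease is a secondary aim (section 1.2). Section 4.5.1.2 justifies the narrower follow-up by saying that most side effects end with washout or are negligible, and it lists osteoporosis/fracture and cardiovascular disease among the exceptions. On the ischaemic events of the adjuvant trial, section 5 says: "The observed difference was mainly due to more reports of angina pectoris". Angina is therefore a component that registry follow-up should be able to identify by name.

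**Working it through.** No sample size, power or alpha figure is involved, so the check is a row-by-row comparison. The protocol names ICD-10 as its code system but does not print the headings. The meanings below are the standard headings and are an assumption to that extent.

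| Event named in 4.5.1.2, 4.5.4.2 or 6.2 | Table 1 | Result |
|---|---|---|
| Angina | No row; I20 (angina pectoris) sits under hypertension | Mislabelled or not captured |
| Hypertension | I20, I15 (secondary hypertension), I27 (other pulmonary heart disease, including pulmonary hypertension); I10 (essential hypertension) absent | Essential hypertension missed as written |
| Phlebitis, superficial thromboembolism | Only I80.2 (deep) and pulmonary embolism | No row |
| Osteoporosis | M80 (osteoporosis with fracture), under fractures; M81 (without fracture) absent | Reached only once a fracture occurs |
| Stroke, any type | I63, I64; haemorrhagic codes I60 to I62 absent | Narrower than the event asked for |
| Heart attack, TIA, deep vein thrombosis, pulmonary embolism, fracture, other cancers | Own rows | Covered |

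The absence of rows for angina, phlebitis and osteoporosis can be seen from the protocol alone. The hypertension and stroke results also need the ICD-10 headings.

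The hypertension row has two possible readings:

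1. I20 is meant literally. Registry angina is then labelled hypertension, and essential hypertension is missed.
2. I20 is a slip for I10. The row itself hints at this: I20 is its only code not followed by a note on sub-codes, and I10 has none. Essential hypertension is then captured, but angina is not captured at all.

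On neither reading does closed-site registry follow-up identify angina as angina. Open sites still ask about it on the post-treatment form (4.5.1.2). Ascertainment of angina, of hypertension on the first reading, and of any cardiovascular composite containing them therefore depends on the data source.

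In sum, three named events have no row of their own (angina, phlebitis, osteoporosis), one row carries doubtful codes (hypertension) and one is narrower than its event (stroke). The protocol gives no rates for these events, so the number lost or mislabelled cannot be calculated.

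**The case against.** The strongest reply is that this turns on one digit in a machine-read table and on code meanings that the protocol does not print. A misread of I10 cannot be excluded. That is why neither reading is asserted here as fact; the missing angina row stands on both.

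A second reply is that Table 1 was meant to be narrower, since its purpose sentence in 4.5.1.4 and the aims in section 1.2 name neither osteoporosis nor phlebitis. Those two omissions do conflict with 4.5.1.2, 4.5.4.2 and 6.2 rather than with the aims. But the purpose sentence does not name venous thromboembolism either, and Table 1 has rows for it, so the sentence does not mark a deliberate boundary. A third reply is that 4.5.4.3 already calls the listing unverified. The limitations it states concern seriousness and relatedness, not missing kinds of event.

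Several stronger conclusions are tempting and are not supported:
- A reader might infer that the angina signal is lost for good. Section 4.5.1.4 keeps the raw extracts as source data, so re-matching can recover events unless the provider filters by code, which the protocol does not say.
- A reader might infer that open-site and registry data cannot be pooled. Infarction, fracture and the other covered events are not affected. The same list applies to both arms and randomisation is stratified by hub centre, so no bias between arms is shown.
- A reader might size the defect from Table 5 (ischaemic cardiovascular disease 2.5% v 1.9%). Those figures compare anastrozole with tamoxifen in another trial. Section 5 calls the difference not significant and links it to pre-existing ischaemic heart disease. They do not measure anything lost here.
- A reader might take the defect to cover all follow-up. Before amendment 60 the questionnaires were completed at all sites, and at open UK sites the registries only support site reports.

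**Conclusion.** The point holds as a mismatch between the registry code list and the protocol's own events of interest, together with a hypertension row that needs correction on either reading. Followed as written, the plan yields incomplete or mislabelled secondary (cardiovascular) and safety data from closed UK sites, and a yearly listing short of the 4.5.1.2 events. The primary breast cancer endpoint is not touched: breast cancers have their own codes and are screened in their own right, as are deaths. The harm is lost or mislabelled events and ascertainment that differs by data source.

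This rests on two assumptions: the standard ICD-10 headings apply, and Table 1 is used as sections 4.5.1.4 and 4.5.4.3 describe. It should be fixed before the cardiovascular and safety results are analysed. It does not threaten the trial's main conclusion.

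**What to change.** - Check the hypertension row against the source file and correct it: include I10, and take I20 and I27 out of it.
- Give angina (I20) its own row.
- Add codes for superficial phlebitis and other venous thrombosis (the rest of I80, and I82), osteoporosis without fracture (M81) and haemorrhagic stroke (I60 to I62). Alternatively, state that these are not collected from registries, and align the reporting sentence in 4.5.4.3 with that.
- Re-run the match on the raw extracts already held.

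The cost is a table edit and a re-run of the match. If a registry provider filters by code before release, a variation to the data request is also needed.
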